## Abstract

**Background:**

Type 1 Brugada syndrome (BrS) is a hereditary arrhythmogenic disease showing peculiar electrocardiographic (ECG) patterns, characterized by ST-segment elevation in the right precordial leads, and risk of Sudden Cardiac Death (SCD). Furthermore, although various ECG patterns are described in the literature, different individual ECG may show high-grade variability, making the diagnosis problematic. The study aims to develop an innovative system for an accurate diagnosis of Type 1 BrS based on ECG pattern recognition by Machine Learning (ML) models and blood markers analysis trough transcriptomic techniques.

**Methods:**

The study is structured in 3 parts: (a) a retrospective study, with the first cohort of 300 anonymized ECG obtained in already diagnosed Type 1 BrS (75 spontaneous, 150 suspected) and 75 from control patients, which will be processed by ML analysis for pattern recognition; (b) a prospective study, with a cohort of 11 patients with spontaneous Type 1 BrS, 11 with drug-induced Type 1 BrS, 11 suspected BrS but negative to Na + channel blockers administration, and 11 controls, enrolled for ECG ML analysis and blood collection for transcriptomics and microvesicles analysis; (c) a validation study, with the third cohort of 100 patients (35 spontaneous and 35 drug-induced BrS, 30 controls) for ML algorithm and biomarkers testing.

**Discussion:**

The BrAID system will help clinicians improve the diagnosis of Type 1 BrS by using multiple information, reducing the time between ECG recording and final diagnosis, integrating clinical, biochemical and ECG information thus favoring a more effective use of available resources.

*Trial registration* Clinical Trial.gov, NCT04641585. Registered 17 November 2020, https://clinicaltrials.gov/ct2/show/NCT04641585

## Background

Brugada Syndrome (BrS) is a hereditary arrhythmogenic disease with an electrocardiographic (ECG) pattern characterized by ST-segment elevation in the right precordial leads and burdened by the risk of sudden cardiac death [1]. The prevalence of the syndrome is estimated to be 15 per 10,000 in South East Asia, including Japan, and 2 per 10,000 in the Western countries. BrS has been considered responsible for 4–12% of all sudden deaths and up to 20% of sudden deaths in patients with structurally normal hearts. It is 8 to 10 times more prevalent in men than in women. In a recent meta-analysis, the incidence of arrhythmic events (sustained VT or VF or appropriate implantable cardioverter defibrillator (ICD) treatment or sudden death) in patients with Brugada syndrome was 13.5% per year in patients with a history of sudden cardiac arrest, 3.2% per year in patients with syncope and 1% per year in asymptomatic patients [2]. As more data become available, the currently accepted percentages of Sudden Cardiac Death (SCD) due to BrS need to be updated to establish the real incidence of the syndrome in unexpected deaths in different populations [3].

In these last years, the research interest on BrS has significantly increased since it prevalently affects healthy young adults during their most productive years [1]. Due to its genetic component, there is a need to identify other potentially affected relatives, focusing on children [4].

There are three types of ECG changes associated with Brugada Syndrome. Type 1 shows, in more than one right precordial lead, a coved shape of the ST-segment with J wave or ST-elevation of ≥ 2 mm (mV) at its peak followed by a negative T wave with little or no isoelectric interval; in Type 2, the ST segments have a high take-off but the J amplitude of ≥ 2 mV rises to a gradually descending ST-segment remaining ≥ 1 mV above the baseline followed by a positive or biphasic T wave; these abnormalities result in a saddle-back configuration. Finally, Type 3 presents ST elevation on the right precordial leads < 1 mm (saddle-back type or coved morphology).

From a diagnostic point of view, BrS can be confirmed in non-diagnostic cases by developing the peculiar ECG patterns in V1 and V2 after administration of Na + channel blockers (i.e., ajmaline, flecainide) [5].

In addition to recognizing specific ECG patterns, genetic and environmental modulators of BrS have been identified, which play a significant role in the dynamic nature of BrS patients' ECG. In 1998 the first genetic mutation in the SCN5A (sodium voltage-gated channel alpha subunit 5) gene was associated with BrS within a family [6]. SCN5A is responsible for phase 0 of the cardiac action potential, and pathogenic variations result in the sodium channel inability to function properly. Since the identification of the first gene associated with BrS, reports of other families affected by BrS have confirmed that the disease genetic origin follows an autosomal dominant pattern of inheritance. More than 250 pathogenic variations associated with BrS have been described in 18 different genes, primarily encoded for sodium, potassium, calcium channels, or proteins associated with these channels [7]. Pathogenic variations in genes encoding desmosomal proteins have also been associated with BrS [8, 9]. Despite these ongoing developments in understanding the genetic causes of BrS, only 30–35% of clinically established cases are genetically diagnosed, and most of these (25–30%) result from pathogenic alterations in SCN5A [5]. The remaining cases may be attributable to alterations in one of the other BrS-associated genes [10]. A recent study [11] concluded that BrS ECG pattern appears not to be a pure Mendelian disorder, but rather the result of different molecular pathologies. Thus, genetic screening results do not currently influence prognosis or treatment [2], since they take into account only a part of the reported cases and variants previously classified as pathogenic may be of ambiguous significance following recent guidelines of the American College of Medical Genetics [12].

Due to disease heterogenicity in terms of genetic and phenotypic features, the use of new approaches as omics (genomics, transcriptomics, proteomics) might assume an important role in understanding the molecular mechanisms and identification of diagnostic/prognostic markers of BrS. These high-throughput technologies produce a considerable amount of data on analyzed genes, RNAs, and proteins, providing a more thorough picture of the different molecular events involved in the disease pathogenesis. In particular, omics technologies can identify new molecular mechanisms through the in-depth analysis of biological (or biochemical) pathways. This information can be extracted to differentiate BrS from similar phenocopies and develop new and reliable biomarkers for disease detection [13]. Among all techniques, the analysis of RNA profile trough transcriptomics has shown its importance in the study of several diseases [14]. This group of molecules is close to patient phenotype and can provide information on patients' condition that standard biochemical analysis or DNA variants cannot detect [15]. RNAs and their associated pathways could represent the bridge between environmental factors and genotype [16], showing the dynamic interaction during the patient's life. Among RNA molecules sub-groups, a prominent role is assumed by non-coding RNAs, particularly the micro-RNAs (miRNAs). These short coding RNA sequences can be found in the so-called microvesicles, a class of membrane vesicles ranging in size between 100 and 1000 nm in diameter, generated by outward budding or blebbing of the plasma membrane [17] during various processes and stimuli [18]. miRNAs modulate gene function by binding with specific sequences of target genes [15]. While transcription factors play a critical role in controlling ion channels/transporters at the transcriptional level, miRNAs are paramount for expression regulation at the post-transcriptional level. These small non-coding RNAs finely regulate the expression of genes. In cardiovascular disease, miRNAs analysis has assumed a leading role in several cardiovascular pathologies [19, 20].

Challenges and actual controversies do exist as far as BrS diagnosis is concerned. Although at a clinical level BrS presents specific ECG features and these criteria have a wide consensus as underlined by present guidelines [21], difficulties exist on ECG interpretation due to the extreme variability of ECG patterns that may change with time and during situations as sleep, fever and vagal stimulation [4, 5]. In contrast to diagnostic criteria for the long QT syndrome, one of the main difficulties in BrS diagnosis is the absence of exact cut-off values to base a clear-cut diagnosis.

The interpretation of these ECG patterns may vary between clinicians since different pathologies can be associated with ST-segment elevation in the right precordial leads (Table 1) [22].

**Table 1 Tab1:** List of pathologies showing an ST-segment elevation in ECG patterns

Pathologies with ST-segment elevation in the right precordial leads
ST-elevation secondary to LVH
ST-elevation secondary to conduction defect (such as left bundle branch block and non-specific intracardiac conduction delay)
Normal variant of ST elevation
Early repolarization pattern (notched J-point typically in anterolateral leads)
Takotsubo (apical ballooning) syndrome
Spontaneously re-perfused STEMI
Wolf-Parkinson-White syndrome (pre-excitation)
Aneurysm/old myocardial infarction
Pericarditis/myocarditis
Hyperkalemia
Hypercalcemia

Even if specific ECG patterns are described in scientific literature, they may vary in the same individual, making the diagnosis problematic [23]. The very low prevalence of the disease associated with the high observer inter-variability in ECG interpretation and the absence of univocal "genetic makers" may lead to a reduced recognition of BrS in the population, potentially increasing risks, including sudden death.

The BrAID (Brugada syndrome and Artificial Intelligence applications to Diagnosis) project aims to integrate classic clinical guidelines for BrS diagnosis evaluation with transcriptomics approach and innovative ML algorithms for ECG pattern recognition: the combined information should lead to new diagnostic strategies in cardiovascular precision medicine of this disease.

## Methods/design

### Study design and population

The study is multicentric, non-randomized and no-profit. Patients with BrS will be enrolled at Fondazione Toscana Gabriele Monasterio, U.O.C. Cardiologia Ospedale San Donato, Azienda Usl Toscana Nord Ovest U.O.C. Cardiologia Ospedale Versilia, Azienda Ospedaliera Universitaria Careggi SOD Aritmologia, Azienda Ospedaliero Universitaria Pisana Cardiologia 2 U.O.C. Cisanello.

The protocol recognizes three phases: retrospective, prospective and validation studies. The prospective and validation studies' enrolment duration will be 24 months and will start during January 2021.

The ECG diagnosis of BrS will be strictly based on the recommendations of the 2015 European Society of Cardiology guidelines for the management of patients with ventricular arrhythmias and the prevention of SCD [2]. Inclusion criteria for BrS patients enrolment, both for the prospective and the validation study, are represented by Type 1 BrS (Coved) electrocardiographic changes, either spontaneous or induced by ajmaline/flecainide test [24, 25] or in the presence of high clinical suspicion (familiarity for BrS, patients who survived cardiac arrest with no apparent cause); age between 14 and 65 years. The control group will be represented by subjects of comparable age who undergo a cardiological examination as outpatients and present a normal baseline ECG. The presence of structural cardiac disease or concomitant diseases that may impair the completion of the protocol, lack of informed consent, pregnancy, history of coronary artery disease, severe renal or hepatic insufficiency will represent the exclusion criteria. Structural heart disease will be excluded in all patients before enrolment by non-invasive imaging (echocardiography and/or cardiac MRI).

The retrospective study aims to train the Machine Learning algorithms for BrS ECG patterns recognition; the prospective study is finalized to collect blood samples for disease-associated biomarkers by transcriptomic and microvesicles analysis, refine the ECG ML algorithm previously developed and integrate this data in the risk stratification algorithm; the validation phase will test the biomarkers discovered in the prospective study, the ECG ML algorithms and the stratification risk in a new cohort of patients.

For the retrospective phase, the ECG traces of about 300 patients (75 with spontaneous BrS, 150 with suspected BrS and 75 controls), with standard recording parameters (speed paper 25 mm/s, amplification of 10 mm/mV, sampling rate 10 s of ECG at 500 Hz, filters: 0.5–100 Hz) will be provided in an anonymized format to the Computer Science Department of the University of Pisa for ML analysis (Fig. 1).

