**Fig. 2 Fig2:**
[figure not shown]
SPIRIT figure of retrospective and validation BrAID study

For the validation phase a new cohort of 100 patients, of which 30 control subjects and 70 subjects (35 spontaneous BrS and 35 suspected), will be enrolled and undergo the same clinical examinations of prospective phase (Fig. 2).

The studies will be performed following the Declaration of Helsinki; they were already approved by the Comitato Etico Area Vasta Nord Ovest, Pisa, Italy. Blood tests and analyses will follow the guidelines of the Human Tissue Act (2004). The trial was registered in ClinicalTrials.gov (Identifier: NCT04641585).

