### Statistical analysis

For the sample calculation, reference will be made to compare sequenced RNAs, using a two-tailed Student's test for independent data. Considering the technology used to obtain RNA data [32], an expression variation of 6 (fold change) being expected, and assuming a gene coverage depth of 0.75 with a standard deviation of 1, a power of 80% and an alpha of 0.05 will be guaranteed by a sample of 11 subjects per group: 11 spontaneous BrS, 11 Suspected BrS (positive), 11 Suspected BrS (negative), 11 Control.

For bioinformatics analysis of transcriptomics, a case calling and demultiplexing will be performed raw processing data for both format conversion and demultiplexing by the Bcl2Fastq 2.20 version of the Illumina pipeline. Reads deduplication based on the unique molecular identifier (UMI) composed of 8 random bases for unambiguous identification of unique library molecules will discriminate between true PCR duplicates and independent adaptor ligation events to fragments with the same start site. DESeq2 will be used to perform comparisons between expression levels of genes and transcripts. Normalization will be performed using the median-of-ratios method [33]. An initial list of modulated genes in the current experimental set will be determined by applying a likelihood ratio test [34]. Adjusted *p*-value < 0.01 will be set an initial threshold. Further analyses on pairwise comparison will be obtained by filtration of the Fold Change (FC) calculation: the ratios between the relative expression values of two different conditions, expressed as the absolute value, will be assessed above 3.

Regarding the predictive models of Machine Learning, the sample numbers for the retrospective study (n = 300) and the final validation study (n = 100) correspond to the number of cases already classified by the clinical centers as Brugada syndrome, the former, and which can be collected during the experimental activities of the project by the same units, the latter. According to the activities foreseen in the trial, validation methodologies (cross-validation techniques) that will exploit this availability of data to develop and estimate the predictive models consistent with state of the art will be prepared [35].

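### Controls need only be of comparable age although BrS is stated to be 8 to 10 times more prevalent in men, so an expected sex imbalance between BrS and control groups is not prevented.

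*Protocol article*

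**What the plan says.** The control definition is in the protocol article, Study design and population: "The control group will be represented by subjects of comparable age who undergo a cardiological examination as outpatients". The same sentence also requires their ECG at baseline to be normal. It follows directly on the inclusion criteria for the prospective and validation studies and is not limited to either. For patients the only demographic limit is "age between 14 and 65 years".

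The Background says of BrS: "It is 8 to 10 times more prevalent in men than in women".

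The group sizes are:
- retrospective: "75 with spontaneous BrS, 150 with suspected BrS and 75 controls", with no selection rule given for the control traces;
- prospective: "11 spontaneous BrS, 11 Suspected BrS (positive), 11 Suspected BrS (negative), 11 Control";
- validation: "30 control subjects and 70 subjects (35 spontaneous BrS and 35 suspected".

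Under Statistical analysis, "DESeq2 will be used to perform comparisons between expression levels of genes and transcripts". A likelihood ratio test with adjusted p below 0.01 gives the first gene list, and pairwise comparisons are then filtered at a fold change above 3. The terms of the full and reduced models are not given.

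Sex is not mentioned in control selection, in either analysis or in the Limitations. Pregnancy is an exclusion, but that does not balance the groups.

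**The concern.** The article fixes a comparability rule and puts age alone in it, while reporting a strong male excess in the disease. Cardiology outpatients with a normal ECG have no evident reason to be 90% men. If they are not, BrS and control groups differ in sex as well as in disease, and a transcript that depends on sex can show a group difference with no disease effect.

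This bears first on the biomarker outcome, and through it on the integrated risk system. A validation cohort normally guards against such artefacts. Here its controls come under the same rule, so a sex-driven difference could recur there and look like confirmation.

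The question belongs to the protocol because it concerns who is recruited. Later analysis can repair it only in part.

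**Working it through.** **The plan's own figure.** The article gives no figure on sex balance. Its one calculated figure, 11 per group, is an input here. A count-data formula comes close to it: n = 2(1.960 + 0.842)² × (1/0.75 + 1²)/(ln 6)² = 11.4, reading the stated standard deviation as a biological coefficient of variation. Nothing below depends on this.

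**Inputs.**
- Men to women among BrS cases: r = 8 to 10 (Background).
- Group sizes: 11 per group (Statistical analysis).
- Fold-change cut: 3 (Statistical analysis).
- Share of men among controls, q: not stated. Assumed 0.40 to 0.60, with about 0.90 as the sex-matched case.

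**1. Share of men among cases.** p = r/(r + 1): 8/9 = 0.889 and 10/11 = 0.909.

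**2. How well sex alone separates BrS from controls.** Balanced accuracy = 0.5 + (p − q)/2.

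| q | p = 0.889 | p = 0.909 |
|---|---|---|
| 0.40 | 0.744 | 0.755 |
| 0.50 | 0.694 | 0.705 |
| 0.60 | 0.644 | 0.655 |
| q = p | 0.500 | 0.500 |

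**3. Transcript expressed only in women.** Expected control/BrS ratio = (1 − q)/(1 − p).

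| q | p = 8/9 | p = 10/11 |
|---|---|---|
| 0.40 | 0.60 × 9 = 5.4 | 0.60 × 11 = 6.6 |
| 0.50 | 0.50 × 9 = 4.5 | 0.50 × 11 = 5.5 |
| 0.60 | 0.40 × 9 = 3.6 | 0.40 × 11 = 4.4 |

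The ratio falls to 3 when 1 − q = 3(1 − p), that is at q = 0.67 (p = 8/9) or q = 0.73 (p = 10/11).

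**4. Transcript expressed only in men.** Expected BrS/control ratio = p/q, from 0.889/0.60 = 1.5 to 0.909/0.40 = 2.3. This is below the cut throughout.

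**5. Transcript s times higher in women.** Expected ratio = [q + (1 − q)s]/[p + (1 − p)s]. At q = 0.50, s = 6 gives 2.25 to 2.41, which fails the cut. Setting the ratio to 3 gives s of about 13 (p = 8/9) or 10 (p = 10/11). At q = 0.60 the values are about 31 and 17. Only strongly female-dominant transcripts pass in expectation.

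**6. What adjustment could rest on.** Expected women in a BrS group of 11: 11/9 = 1.2 or 11/11 = 1.0. The binomial chance of at most one woman is 65-74%, and of none 27-35%.

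**Not modelled.** A transcript must also reach adjusted p below 0.01. Steps 3 to 5 are expected ratios, and samples of 11 will scatter around them.

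**The case against.** A reader might infer more than the article supports, in four ways.

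- **That sex is confounded with disease as a settled fact.** The sex mix of controls and of enrolled cases is not given. The 8 to 10 ratio describes BrS prevalence, and drug-induced or suspected cases may be less male. At 80% men among cases and 50% among controls, balanced accuracy is still 0.65, but the female-only ratio falls to 0.5/0.2 = 2.5, below the cut. For validation, assuming 63/70 against 15/30 men gives Fisher p = 0.00003. That treats all 70 as BrS and only restates the assumed mix. The text supports an imbalance that is expected and not prevented.
- **That the network will learn sex as a BrS feature.** The article gives no ECG difference by sex. The balanced accuracy above is for sex known exactly, not inferred from a trace. Controls have normal ECGs, so the overt pattern already separates spontaneous cases from them.
- **That sex-dependent transcripts in general will be reported as biomarkers.** In expectation the cut of 3 removes moderate effects and all male-only ones.
- **That the analysis omits sex.** The model terms and sex-specific reporting of ML performance may sit in a fuller document that is not shown, so their absence is no finding.

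The drug-test-negative group is also a separate comparator. Its sex mix is not stated, it is not drawn from the outpatient controls, and nothing here applies to its contrast with the drug-positive group.

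All of this limits the size and reach of the point. It does not answer the selection rule: the article states that rule, confines it to age, and reports the sex ratio that makes age insufficient. An unseen analysis plan could add sex as a covariate, but with about one woman expected per BrS group it would have little to work with.

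**Conclusion.** The point holds as a gap in control selection. Following the stated rule, a sex imbalance between BrS and control groups is expected unless outpatient controls happen to be about 90% men, and nothing in the article secures that.

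If cases are 89-91% men and controls 40-60% men, sex alone separates the groups with balanced accuracy of about 0.64-0.76. A female-only transcript has an expected group ratio of about 3.6-6.6 against a cut of 3. The case share rests on the article's ratio applying to enrolled patients, and the control share is an assumption. The biomarker consequence is confined to strongly female-dominant transcripts. For the ECG model it is a risk without a figure.

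The validation cohort may fail to expose a sex-driven finding. The documents do not show that it must repeat one. The change should be made because it is cheap and recruitment fixes the matter.

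**What to change.** In Study design and population, require controls to be of comparable age and sex, frequency-matched to the BrS patients, in the prospective and validation phases. Select the 75 retrospective control traces by the same rule. With the control share of men equal to that of the cases, balanced accuracy from sex alone is 0.50 and the expected group ratio for a purely sex-driven transcript is 1.0.

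As a supporting step, put sex in both the full and the reduced DESeq2 model, so that the likelihood ratio test is for group given sex. This cannot replace matching, because so few women are expected in each BrS group.

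The cost is slightly slower control recruitment and one degree of freedom among 44 subjects. Matching itself does not change the 11 per group.
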